### Sample size calculation

A meta-analysis of 50 RCTs evaluating single-session adolescent psychological health interventions [41] reported a mean effect size of Hedges *g* = 0.32, which can be interpreted as a small-to-medium effect size (small effect size = 0.2; medium effect size = 0.5). This is consistent with findings from the RCT evaluation of *Dove Confident Me: Single Session* [36], which reported standardised effects ranging from small to small-to-medium for outcome measures. Based on a more conservative, lower bound of d = 0.2, a sample size of *n* = 500 girls and *n* = 500 boys per arm would provide in excess of 95% power over any positive range of correlation between baseline and outcome data at T2 and would have in excess of 90% power for separate analyses for girls and boys. We will oversample to mitigate the effects of loss to follow-up due to student absence or technical difficulties to increase population coverage and external validity. Therefore, the target study sample size will be approximately 2000 adolescents: 1000 (500 girls, 500 boys) in the control condition, 1000 (500 girls, 500 boys) in the intervention condition. It is estimated that 20 eligible schools will be recruited to achieve this sample size.

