### Study design

The main study consists of a two-arm open parallel group cluster RCT with an intervention group and a lessons-as-usual wait-list control group. Stratifying based on school size (large, medium, small), randomisation of schools will be conducted by an independent researcher blinded to conditions through block randomisation, using random block sizes of two, four, and six. Randomisation of schools will be completed following confirmation that schools recruited to the trial meet eligibility criteria, and the school principal has provided informed consent.

Cimigo and the study research team (i.e., study authors) will be informed of the study allocation, though will be blind to the size of each block during randomisation to minimise selection bias [56]. Participants will not be explicitly told their study condition, though will be made aware of the assessment time points and whether they receive the lesson between T1 and T2 (intervention) or after T3 (wait-list control). The statistician will be blinded to conditions during the trial and analysis. The trial will have assessments at baseline, post-intervention, and two-month post-intervention time points; see Fig. 1 for a flow diagram.

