### Strengths

A core strength of this project is the participatory approach adopted by the multi-stakeholder project team, which has led to careful, culturally-sensitive co-creation of the intervention and provides opportunity for widespread dissemination across the country. Embedded within UNICEF Indonesia’s LSE curriculum, *Dove Confident Me Indonesia: Single Session * is projected to reach hundreds of thousands of adolescents attending state-run junior high schools by the end of 2022. This meets calls for intervention research to centre implementation planning at the core of development and design from both within the field of body image [66] and mental health practice more broadly [47]. By embedding our intervention within an established, acceptable framework and dissemination modality (i.e., UNICEF Indonesia’s LSE) we are ensuring the programme is set up for widespread dissemination and implementation. Importantly, as the dissemination plan has already been arranged with project stakeholders, namely UNICEF and the Dove Self-Esteem Project, a due-diligence contingency plan to remove the body image lesson from the current version of UNICEF Indonesia’s LSE programme has been arranged should the results from this trial indicate the programme has unintended negative effects on adolescent well-being upon full analysis. However, given that this intervention is based on an existing evidence-based intervention and has been carefully co-created by international and local experts, teachers, and school children, we are confident it will have the hypothesised positive effects on adolescents’ well-being.

Relatedly, we have task-shifted the delivery of the intervention to community providers (i.e., teachers and school guidance counsellors). Again, this a crucial strategy in enhancing wide-scale dissemination and ensuring intervention sustainability in contrast to relying on highly trained specialist providers [67–69]. Additional strengths of this study design are the use of a cluster RCT design and the large sample size. The cluster RCT design helps circumvent contamination of the control group [52] and the targeted 2000 participants will ensure adequate power to this study, while accounting for potential participant drop-out at follow-up time points.

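### The stated power (>95% pooled, >90% per gender at d = 0.2) makes no allowance for randomising about 20 schools, so the design does not assure it

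*Protocol article*

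**What the plan says.** All references are to the protocol article.

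- **Study design:** "The main study consists of a two-arm open parallel group cluster RCT", and "randomisation of schools will be conducted by an independent researcher blinded to conditions through block randomisation".
- **Sample size calculation, inputs:** "Based on a more conservative, lower bound of d = 0.2", with a target of "1000 (500 girls, 500 boys) in the control condition, 1000 (500 girls, 500 boys) in the intervention condition".
- **Sample size calculation, pooled claim:** this sample "would provide in excess of 95% power over any positive range of correlation between baseline and outcome data at T2".
- **Sample size calculation, claim by gender:** the same sentence adds a second figure, namely that the sample "would have in excess of 90% power for separate analyses for girls and boys".
- **Sample size calculation, clusters:** "It is estimated that 20 eligible schools will be recruited to achieve this sample size". The reasons given for oversampling are loss to follow-up, population coverage and external validity. Clustering is not among them.
- **Strengths:** "the targeted 2000 participants will ensure adequate power to this study".
- **Data analysis:** models are to be fitted both with and without clusters as random effects. The T2 and T3 comparisons use ANCOVA, ignoring gender, split by gender, and with gender as a factor.

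The only ICC in the article is in Intervention fidelity, where it measures agreement between lesson assessors. It says nothing about how alike students of one school are on the outcome.

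**The concern.** When whole schools are randomised, students in the same school share part of their outcome variation, and the effective sample is smaller than the number of students. The power statement uses three inputs: effect size, students per arm and baseline correlation. The number of schools appears only as a recruitment estimate. The pooled claim is also worded as a guarantee over every positive correlation, so it can be checked against the stated design whatever a fuller document may contain.

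The stake is how a null or imprecise result is read. Readers told that power exceeds 95% would take a null as good evidence against an effect of 0.2. The girls-only and boys-only comparisons are prespecified, and each rests on half the students from the same 20 schools.

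**Working it through.** **Inputs from the article.** d = 0.2 (SD 1); 1000 students per arm, 500 of each gender; 20 schools. I take 10 schools per arm, so m = 1000/10 = 100 students per school, or 50 of one gender.

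**Assumptions, not given in the article.** Two-sided 5%; equal school sizes; no attrition; ICC between 0.01 and 0.05; baseline correlation r of 0, 0.5 or 0.7. The ICC here is that of the baseline-adjusted outcome.

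**Step 1: the plan's own figures, students independent.** SE = √(2(1 − r²)/n), power = Φ(d/SE − 1.96).

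- Pooled, n = 1000, r = 0: SE = √(2/1000) = 0.0447; d/SE = 4.47; power 99.4%. Power rises with r, so the claim of more than 95% holds over every positive r.
- Per gender, n = 500, r = 0: SE = √(2/500) = 0.0632; d/SE = 3.16; power 88.5%. It reaches 90% at r of about 0.22 and 95.5% at r = 0.5.

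So the pooled claim is consistent with an individually randomised calculation. The per-gender claim fits one only if r is at least about 0.22.

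**Step 2: 20 schools.** SE = √(2(1 − r²)(1 + (m − 1)·ICC)/n). Power comes from the noncentral t distribution with 20 − 2 = 18 degrees of freedom (critical value 2.101).

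Worked case, pooled, ICC 0.02, r = 0.5: design effect = 1 + 99 × 0.02 = 2.98; SE = √(2 × 0.75 × 2.98/1000) = 0.0669; d/SE = 2.99; power 81%.

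| ICC | Design effect, pooled | Pooled power, r = 0 / 0.5 / 0.7 | Design effect, per gender | Per-gender power, r = 0 / 0.5 / 0.7 |
|---|---|---|---|---|
| 0.01 | 1.99 | 85 / 93 / 99% | 1.49 | 69 / 81 / 93% |
| 0.02 | 2.98 | 69 / 81 / 93% | 1.98 | 57 / 69 / 85% |
| 0.05 | 5.95 | 41 / 52 / 68% | 3.45 | 36 / 46 / 62% |

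**Step 3: the largest ICC at which each claim still holds (t, 18 df).**

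| Claim | r = 0 | r = 0.5 | r = 0.7 |
|---|---|---|---|
| Pooled, 95% | 0.004 | 0.008 | 0.017 |
| Per gender, 90% | none | 0.003 | 0.014 |

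**Step 4: detectable effect, pooled, 90% power, r = 0.5.** d = (2.101 + 1.330) × SE.

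- ICC 0.01: 3.431 × 0.0546 = 0.19
- ICC 0.02: 3.431 × 0.0669 = 0.23
- ICC 0.05: 3.431 × 0.0945 = 0.32

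**Step 5: attrition.** The target of 2000 equals the N in the power statement, so it contains no reserve over that N. The pilot's green threshold is 70% completion to T2 (Table 3). At 70 students per school and ICC 0.02, pooled power falls to 63% (r = 0) or 75% (r = 0.5).

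**The case against.** **The shortfall depends on an ICC the article does not give.** This stands. At ICC 0.01 and r = 0.7, pooled power is 99% and per-gender power 93%, so both claims are met. A reader might infer that the stated power is certainly lost, or that the trial has about even odds of detecting its target effect. The document supports neither. Power near one half for the pooled comparison arises only around ICC 0.05 with r of about 0.5 or less.

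**The effect of 0.2 is deliberately cautious.** Also true. The article cites a mean of 0.32 for single-session interventions. With the Step 2 formula at d = 0.32, pooled power is 97% at ICC 0.02, r = 0, and 89% at ICC 0.05, r = 0.5. But the power claims are attached to 0.2 and must be judged there.

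**The table depends on which ICC is meant.** This stands. The formula needs the ICC of the baseline-adjusted outcome, or equal baseline correlations at school and student level. A raw ICC put into it can understate power. With an assumed raw ICC of 0.02, student-level r = 0.5 and school-level r = 0.8, pooled power is 94%, against 81% in the table.

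**Clustering is handled in the analysis, and the article is condensed.** A reader might infer that the trial ignores clustering altogether. It does not: Data analysis includes models with cluster random effects, and misstated planning power does not by itself bias the estimate. An ICC may also sit in a fuller document, so its absence alone is no fault. Neither point rescues the printed guarantee over any positive correlation, which the stated design does not support.

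**The abstract is a different claim.** Correct. It gives 95% power for small-to-medium effects with a minimum of 1000 participants, and the figures for 2000 students do not test it.

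**Conclusion.** The point holds as a claim about assurance. The stated powers carry no visible allowance for clustering, and a design of about 20 schools does not secure them. The pooled guarantee fails near r = 0 once the baseline-adjusted ICC exceeds about 0.004; at r = 0.7 the ceiling is about 0.017. The per-gender claim has a second weakness unrelated to clustering: it falls short for r below about 0.22 even with independent students.

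The size of any shortfall is unknown, because the ICC and the correlation are both unstated. Over the assumed ranges, pooled power runs from 41% to 99% and per-gender power from 36% to 93%. These figures assume two-sided 5%, 10 equal schools per arm and no attrition; unequal school sizes or losses would lower them.

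**What to change.** In Sample size calculation, restate power or the detectable effect for 20 schools over an explicit range of ICC and baseline correlation, using the design effect and about 18 degrees of freedom. State the significance level, and say whether the ICC is raw or baseline-adjusted. Report the pooled and per-gender figures separately.

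Withdraw the two unconditional claims, including the phrase covering every positive correlation. Bring the adequate-power sentence in Strengths into line. Reconcile the abstract's minimum of 1000 participants with the 2000 (500 of each gender in each of two arms) on which the sample size section bases its claim, naming the effect size the abstract figure refers to.

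If the validation data from over 1000 adolescents record school, they could inform the ICC. The article describes no repeat measurement there, so that value would be raw and should be labelled as such.

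The cost is a rewritten paragraph and two edited sentences. The correction adds no participants or procedures; the stated power becomes less favourable.

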### Data analysis

Data preparation and assessment of baseline equivalence will be undertaken using SPSS 28.0 (IBM Corp, 2021). Data will be screened to ensure coding fidelity and data veracity. Data validity checks will be undertaken, and derived outcome scale data will be examined for the presence of outliers and any unduly inferential observations and to assess the distribution of scores. Analysis will proceed on an intention-to-treat basis. Analysis will be conducted with and without clusters as random effects to determine any significant impact [65]. Missing data will be assessed across outcomes and time points. A sensitivity analysis to missing data will be performed. Attention check data (greater than 70% successful completion of attention checks) will form a per-protocol analysis.

The primary analysis will be a linear mixed model with random intercepts. The model will include the three main effects, three two-way interactions, and three-way interaction for randomised arm (between-subjects fixed effect factor with two levels intervention and control), study phase (repeated measures fixed effect factor with two levels T2 and T3), gender (between-subjects fixed effects factor with two levels, male and female), including a baseline measure as a covariate, and the three two-way interactions between covariate and each of randomised arm, gender, and phase. A priori analyses will proceed primarily comparing the two randomised arms at T2 controlling for baseline covariate (a) ignoring gender (b) split by gender and (c) incorporating gender as a factor. These analyses will be repeated at T3. These prior reasoned analyses will use ANCOVA. The ANCOVA model will be extended to include a baseline by randomised arm interaction term if the homogeneity of regression lines assumption is not tenable. All models will be screened for gross deviations from underpinning assumptions to ensure valid statistical inferences are drawn.

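### Schools are randomised, but the plan analyses with and without clusters and does not say which version is confirmatory

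*Protocol article*

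**What the plan says.** The Study design section describes a "two-arm open parallel group cluster RCT with an intervention group and a lessons-as-usual wait-list control group" and states that "randomisation of schools will be conducted by an independent researcher blinded to conditions through block randomisation". The Sample size calculation section adds: "It is estimated that 20 eligible schools will be recruited to achieve this sample size", and sets 1000 students per arm.

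The Data analysis section has three statements that bear on clustering:

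- A general rule, given before any model is named: "Analysis will be conducted with and without clusters as random effects to determine any significant impact".
- The primary model: "The primary analysis will be a linear mixed model with random intercepts". Its repeated factor is study phase (T2 and T3). The level of the intercepts (student, class or school) is not stated.
- The a priori comparisons of the arms at T2, repeated at T3, overall and by gender: "These prior reasoned analyses will use ANCOVA". No school term is named for them.

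No school-level ICC or design effect for the outcomes appears anywhere. The only ICC in the protocol concerns inter-rater agreement on lesson fidelity.

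**The concern.** When schools are randomised, the arm comparison varies with school-to-school differences as well as student-to-student differences. School therefore belongs in the inference by design, not because a check on the data finds it important. The plan commits to running the analysis both ways and gives no rule for which result counts. That leaves three outcomes open: the unclustered p-value is reported, the school term is dropped when it looks unimportant, or the choice is made after both results are seen.

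The two model statements do not settle it. A student intercept would handle the two repeated measures but would not account for schools. An ANCOVA with no school term treats schoolmates as independent.

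At stake is the validity of the standard errors and confidence intervals for body esteem and the secondary outcomes. The Strengths section ties this trial to a nationwide roll-out, with a contingency to withdraw the lesson if harm is seen. Standard errors that are too small could produce a false benefit or a false harm.

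**Working it through.** **Inputs from the protocol.** 20 schools and 2000 students, 1:1, so about 10 schools per arm and 2000/20 = 100 students per school. One gender gives 500 per arm, or 500/10 = 50 per school. The abstract's minimum of 1000 participants also gives 1000/20 = 50 per school if all 20 schools stay. Planning effect d = 0.2.

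**Assumptions.** Two-sided 5% level (not stated), equal school sizes, and a residual school ICC (given baseline) of 0 to 0.05.

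**Step 1: the plan's own figures.** The protocol gives power but no error rate. Treating students as independent, with baseline–outcome correlation ρ, power = Φ(d/√(2(1−ρ²)/n) − 1.96).

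- n = 1000 per arm, ρ = 0: 0.2/√0.002 = 4.47, giving power 99.4%. The stated figure above 95% reproduces.
- n = 500 per arm, ρ = 0: 0.2/√0.004 = 3.16, giving power 88.5%. It passes the stated 90% once ρ is at least 0.22.

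The overall figure thus reproduces with no allowance for schools.

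**Step 2: false-positive rate when school is ignored.** The true variance of the arm difference is inflated by DE = 1 + (m − 1) × ICC, so the actual rate is 2[1 − Φ(1.96/√DE)]. Example with m = 100 and ICC 0.01: DE = 1 + 99 × 0.01 = 1.99; 1.96/√1.99 = 1.39; rate 16.5%.

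| Residual ICC (assumed) | DE, m = 100 | Rate, m = 100 | DE, m = 50 | Rate, m = 50 |
|---|---|---|---|---|
| 0 | 1.00 | 5.0% | 1.00 | 5.0% |
| 0.001 | 1.10 | 6.2% | 1.05 | 5.6% |
| 0.005 | 1.50 | 10.9% | 1.25 | 7.9% |
| 0.01 | 1.99 | 16.5% | 1.49 | 10.8% |
| 0.02 | 2.98 | 25.6% | 1.98 | 16.4% |
| 0.03 | 3.97 | 32.5% | 2.47 | 21.2% |
| 0.05 | 5.95 | 42.2% | 3.45 | 29.1% |

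**Step 3: check by simulation.** With 20 schools, no true effect and 3000 runs per setting, a baseline-adjusted ANCOVA without school rejected in 10.9%, 17.2%, 25.8% and 41.7% of runs at ICC 0.005, 0.01, 0.02 and 0.05 (m = 100). With m = 50 it rejected in 7.3%, 10.7%, 16.0% and 29.1%. A t-test on baseline-adjusted school means stayed between 4.3% and 5.4% in every setting.

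**Step 4: the school term kept only if significant.** Simulation with a one-way F pre-test, 10 schools per arm and 5000 runs:

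| Residual ICC (assumed) | m = 100 | m = 50 |
|---|---|---|
| 0 | 5.0% | 4.8% |
| 0.002 | 7.2% | 5.2% |
| 0.005 | 7.1% | 6.7% |
| 0.01 | 6.9% | 7.9% |
| 0.02 | 5.4% | 6.9% |
| 0.05 | not run | 5.2% |

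The inflation is small here because the pre-test usually keeps the term when the ICC is large. Taking the smaller of the two p-values instead gives about the same rate as ignoring school (16% at ICC 0.01, m = 100).

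**The case against.** The strongest reply is that the cluster sentence is a general rule. It stands with the intention-to-treat and missing-data rules and is not limited to one model, so a clustered version of each ANCOVA can be read as planned. Its stated purpose is most naturally a check on whether clustering matters, and under that rule the error rate rises to about 8% at most. The mixed model, not the ANCOVA, is named as primary, and its random intercepts may include school. The sentence also cites a source that is not at hand. The exact degrees-of-freedom method and the nesting of classes are commonly left to an analysis plan.

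Much of this stands, and it rules out some stronger readings. A reader might infer that clustering is absent from the ANCOVAs; the text only fails to name a school term for them. A reader might take the ANCOVAs as the headline tests, or as run before the mixed model; the text says only that they focus primarily on T2. A reader might take the mixed model as having student intercepts only; the level is simply not stated.

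The reply does not supply the missing rule. The same paragraph labels the missing-data analysis as a sensitivity analysis but gives the unclustered analysis no such label. Letting the data decide whether school stays in is not a valid basis for inference in a school-randomised trial, even where the inflation is modest.

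**Conclusion.** The point holds as a defect in what the protocol states: it plans two versions of the analysis, one of which ignores the unit of randomisation, and makes neither confirmatory. It should be corrected before analysis because the primary inference depends on it.

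The size is conditional. If the unclustered result is used, the false-positive rate runs from about 6% to 42% with 100 students per school for residual ICCs of 0.001 to 0.05, and from about 8% to 29% with 50 per school for ICCs of 0.005 to 0.05. If the school term is kept only when significant, it is about 5–8%. If the clustered version is used throughout, there is no inflation from this source.

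A reader might infer a general error rate of 15–40%. The protocol does not support that as a flat statement: with 100 students per school it needs a residual ICC of about 0.009 to 0.045 (DE 1.85 to 5.42) and reliance on the unclustered p-value. The protocol gives no ICC and does not commit to that p-value.

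**What to change.** Replace the cluster sentence with a rule to this effect: the analysis with a random intercept for school, with a small-sample degrees-of-freedom correction for about 20 schools, or an equivalent school-level analysis, is the single confirmatory version. It applies to the primary mixed model, which also has a student intercept for the repeated measures, and to all T2 and T3 ANCOVA comparisons, including those split by gender. School is retained whatever its estimated variance, ICC or p-value. Any analysis without clusters is descriptive only.

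The cost is a change of wording; standard mixed-model software fits these models. Confidence intervals will be wider, and correctly so. Power will be lower than stated: with 20 schools of 100, d = 0.2, ρ = 0.5 and a t-test on 18 degrees of freedom, it is about 93%, 81% and 52% at assumed ICCs of 0.01, 0.02 and 0.05. The sponsor should expect this when adopting the rule.

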### Paper and study aims

This paper aims to describe how *Dove Confident Me Indonesia: Single Session* was culturally adapted for use in Indonesian junior high state schools. It details the methods that will be employed to evaluate the intervention’s effectiveness and acceptability in a randomised controlled trial, as well as considerations for conducting this research during the COVID-19 pandemic. It also provides the plan for dissemination and highlights the strengths and limitations of the research trial study design.

The aim of the study outlined in this paper is to evaluate *Dove Confident Me Indonesia: Single Session*, as delivered online to students by schoolteachers or school guidance counsellors working in Indonesian state schools, in terms of intervention effectiveness and acceptability. Although originally designed to be delivered in a face-to-face format in school classrooms, project partners made a collaborative decision to evaluate the effectiveness of the intervention delivered in an online setting (i.e., via virtual video-conferencing classrooms) in response to the ongoing COVID-19 pandemic.^2^ Considering this adaptation, this study aims to assess the acceptability of the curriculum and pedagogy with students and teachers as well as the programme’s effectiveness in improving body esteem and related psychosocial outcomes. In line with previous evaluations of single-session body image interventions [36], we anticipate the intervention to provide short-term (up to two months follow-up) improvements in body image compared to a wait-list control group in order to assess the absolute impact of the intervention. Moreover, in line with the Tripartite Influence Model [51] and the targeted risk factors *Dove Confident Me Indonesia: Single-Session* aims to address, we anticipate a short-term reduction in internalisation of appearance ideals and appearance comparisons, alongside a reduction in the extent to which negative body image prevents adolescents from engaging in life activities relative to the wait-list control group. Finally, due to cultural adaptations of the original programme to challenge harmful skin shade ideals in Indonesia, we anticipate short-term improvements in skin shade satisfaction.

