#### Primary outcome measure: Body esteem

The primary study outcome will be body esteem, a specific component of body image, defined as a person’s self-evaluation of one’s body or appearance [59]. Body esteem will be measured using a culturally adapted Bahasa Indonesia version of the Body Esteem Scale for Adolescents and Adults (BESAA) [59]. Specific items and subscales to be used during the analyses will depend on the findings of the psychometric testing of the measure, as previously described. The self-report items are rated on a five-point Likert-type scale from 1 (never) to 5 (always). Negatively worded items are reverse scored and higher mean scores indicate greater body esteem.

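### The primary mixed model has no named deciding contrast, and T2 and T3 ANCOVAs in three gender versions also have a claim to decide the trial

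*Protocol article*

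**What the plan says.** All places are in the protocol article.

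- **Outcome.** Under the primary outcome heading: "The primary study outcome will be body esteem, a specific component of body image". No time point is attached. On scoring, the same section says: "Specific items and subscales to be used during the analyses will depend on the findings of the psychometric testing of the measure".
- **Aims.** The expectation covers the whole follow-up period: "we anticipate the intervention to provide short-term (up to two months follow-up) improvements in body image compared to a wait-list control group".
- **Primary model.** Data analysis: "The primary analysis will be a linear mixed model with random intercepts". Its fixed effects are arm, phase (T2, T3) and gender with all their interactions, the baseline score, and the interactions of baseline with arm, gender and phase.
- **Further planned comparisons.** The same paragraph continues: "A priori analyses will proceed primarily comparing the two randomised arms at T2 controlling for baseline covariate". The versions are listed as "a) ignoring gender (b) split by gender and (c) incorporating gender as a factor. These analyses will be repeated at T3", and "These prior reasoned analyses will use ANCOVA".
- **Power.** The sample size section takes d = 0.2 with 500 girls and 500 boys per arm. It claims more than 95% power at T2 overall and more than 90% for girls and boys analysed separately.

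**The concern.** One analysis is called primary, but no estimate from it is named as the deciding one. The word *primarily* then goes to a different method at one of the two time points, in three gender versions. The aims point to the whole two months, the power statement to T2, and the power claim also supports gender-specific testing. A reader of the eventual report could not tell from this text whether the trial succeeds on the mixed model or an ANCOVA, at T2 or T3, or on the pooled result rather than that for girls or boys.

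This matters because the lesson is planned for national roll-out, with a contingency to withdraw it if the results show harm (Strengths section). If the deciding result is not fixed beforehand, a favourable one among several can be presented as the planned primary finding.

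**Working it through.** **1. The plan's power figures.** Inputs from the sample size section: d = 0.2, n = 1000 per arm overall and 500 per arm within each gender. Alpha is not stated; 0.05 two-sided is assumed. As a check of the plan's own inputs only, clustering is ignored.

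Power = Φ(d·√(n/2) / √(1 − r²) − 1.96), where r is the baseline–outcome correlation.

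- Overall, r = 0: 0.2 × √500 = 4.472; 4.472 − 1.960 = 2.512; power 99.4%. This agrees with the claim of more than 95%.
- Within gender, r = 0: 0.2 × √250 = 3.162; 3.162 − 1.960 = 1.202; power 88.5%. At r = 0.3 it is 91.2% and at r = 0.5 it is 95.5%. This is close to or above the claimed 90%.

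So both the pooled and the gender-specific comparisons are ones the trial was sized for.

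**2. Whether the mixed model contains the T2 comparison.** Code T2 as the reference phase and one gender as the reference. Let w be the weight given to the other gender and b a baseline value. The model's arm difference is

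- at T2: β(arm) + w·β(arm×gender) + b·β(arm×baseline)
- at T3: the same, plus β(arm×phase) + w·β(arm×phase×gender)

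The T2 contrast can therefore be derived, once w and b are chosen. With this coding and an uncentred baseline, β(arm) alone is the T2 effect in the reference gender at a baseline of zero, which lies outside the 1-to-5 scale. Calling the model primary does not by itself identify one test.

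**3. Counting the ANCOVAs.** Three versions × two time points = 6 analyses. Version (b) holds two tests, so there are 4 arm comparisons per time point and 8 in all. The arm effect in (c) nearly duplicates that in (a). That leaves 3 distinct comparisons per time point (pooled, girls, boys) and 6 in all.

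**4. Error rate if any of them could decide.** Assumptions: no true effect; 5% two-sided per test; any significant result counts; girls' and boys' test statistics independent; pooled z = (z_girls + z_boys)/√2; T2–T3 correlation ρ. Simulation used 1,000,000 draws (400,000 for ρ = 0.8).

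| Tests | ρ | Chance of at least one false positive |
|---|---|---|
| Pooled, girls, boys at T2 | – | 11.5% |
| Same three at T2 and T3 | 0.3 | 21.1% |
| | 0.5 | 20.2% |
| | 0.7 | 18.5% |
| | 0.8 | 17.3% |
| | 0.9 | 15.8% |

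For reference, six independent tests would give 1 − 0.95⁶ = 26.5%. Girls and boys share schools, so their results may be positively correlated, which would lower these figures somewhat.

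**5. After naming one test.** Error is 5% and power stays at 99.4% on the plan's inputs. A fixed testing order leaves that first test unchanged. Bonferroni over six tests (0.05/6 = 0.0083) would instead give 96.7% pooled and 70.0% within each gender at r = 0.

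**The case against.** The best defence is that the text has an order. Only the mixed model is called the primary analysis; the ANCOVAs read as planned follow-up comparisons, with T2 ahead of T3; and the power statement refers to T2. This stands in part. A reader might infer that the trial has two rival primary analyses or no primary hypothesis at all. The documents do not support that: the pooled comparison at T2 is recognisably the leading candidate. It is implied, however, and not fixed.

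Other strong readings also fail:

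- *The mixed model cannot give the T2 comparison.* It can (step 2); the contrast is simply not named.
- *The tests are uncontrolled for multiplicity.* The article is silent on alpha and testing order, and an analysis plan that is not shown may settle both. The error rates are therefore conditional on a decision rule that the article does not state.
- *Gender as a factor adds an interaction test to each ANCOVA.* The interaction is specified for the mixed model only, so no such tests are counted here.
- *Open scoring inflates the error further.* The Measures section says the psychometric work, on a sample of over 1000 adolescents, will be finished before the main trial is analysed. Several co-primary subscales are a possibility, not a plan.
- *The two methods use different students.* ANCOVA needs the given time point, while the mixed model can use either. That is ordinary, and intention-to-treat analysis and a missing-data sensitivity analysis are planned.

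The gender-specific comparisons are also a deliberate design aim, since they were powered. That is a reason to give them a stated place, not to remove them.

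**Conclusion.** The point holds as a defect in what the article states, not in what it omits. A model is named as primary without a deciding contrast, and the adjoining text, the aims and the power statement give other comparisons a claim to that role. If any significant result were accepted, the false-positive chance would be roughly two to four times the nominal level: 11.5% at T2 alone and 17–21% over T2 and T3. These sizes rest on an assumed 5% per test, assumed T2–T3 correlations of 0.8 to 0.3, independent results for girls and boys, and the any-result rule. They show what the wording allows, not what the trial is stated to do. The matter should be corrected; it does not undermine the design.

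**What to change.** 1. Name one primary test: the intervention–control difference in body esteem at T2, averaged over girls and boys and evaluated at mean baseline, as a contrast from the mixed model already called primary. State its significance level.
2. Test the same contrast at T3 next, in a fixed order.
3. Report the arm-by-gender interaction and the gender-specific estimates with confidence intervals as prespecified secondary results.
4. Label the ANCOVAs as supporting or sensitivity analyses.
5. Designate one body esteem score as primary and fix it before outcome data by arm are seen. The scoring work is already scheduled before the main analysis. This tightens the timing, which is worthwhile because the research team knows the allocation and checks data quality during collection.

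The cost is wording in the analysis plan and registry; sample size and data collection do not change. The one loss is that T3 and gender-specific results can no longer be claimed as primary.
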